## Background

Falls are a common and serious problem facing elderly people and are associated with considerable mortality and morbidity [1]. Forty to sixty percent of falls cause injuries with an estimated 5% of incident falls resulting in fractures[2,3]. Falls result in institutionalisation[4], hospitalisation[5] and injury-related death[6]. Over the age of 65 years a third of the population fall at least once a year [7] rising to over a half by 85 years [2]. Previous studies have identified a number of potentially modifiable fall risk factors[1]. Intervention studies in the USA and New Zealand have shown that a combined multidisciplinary assessment and treatment programme and an individualised home based targeted exercise programme respectively can reduce falls by 30%-46% [8-10]. The UK PROFET study showed that in patients presenting to an Accident and Emergency department with a fall, the number of subsequent falls were reduced by half in those who had received the intervention, which constituted a thorough medical assessment and an occupational therapy home visit[11].

In 1999 there were 647,721 A&E attendances and 204,424 admissions to hospitals in the UK as a result of injuries sustained in unintentional falls by the over 60's. It was calculated that these falls cost the UK Government a total of £981 million, £581 million of which was met by the NHS. The main cost components were inpatient admissions (making up 49.4% of total costs) and long term care costs (accounting for 41%). The costs incurred as the result of a fall increased with age[12].

We do not know whether interventions provided to high risk older people identified in primary care are effective, nor whether falls programmes now offered by day hospitals are sufficiently well constituted and intensive to deliver similar benefits to those studies outlined above. Nor do we know if day hospital settings will be acceptable to the 'screened well'. Addressing 'fear of falling' and consequent social isolation or restriction are key features of an effective falls prevention programme. The proposed multi-centre randomised controlled trial will assess whether falls can be successfully and cost-effectively reduced using day hospital facilities.

In addition to assessing the effectiveness of the Day hospital as an intervention to reduce falls it is important to evaluate the intervention in terms of its cost-effectiveness. In a resource constrained health care system it is important to ensure that limited resources are spent in such a way as to maximise outcomes. Within the context of this proposed study the economic objective is to establish whether it is efficient to allocate resources to the Day hospital, in comparison to standard care, as an intervention to reduce falls amongst elderly people. To address the efficiency of putting resources to Day hospitals a cost-effectiveness analysis and cost-utility analysis will be performed.

## Objectives

### Main research hypothesis and question

The main hypothesis to be tested is that a multidisciplinary falls assessment and intervention occurring at a Geriatric Day hospital can decrease the rate of falls over the course of one year, in older people identified in primary care as being at high risk of falling.

### Secondary research questions

1. Can the above intervention reduce the proportion of people with single or recurrent falls (>1)?

2. Can the above intervention reduce fall-related injuries (including fractures)?

3. Can the above intervention reduce disability and improve quality of life?

4. Can the above intervention reduce institutionalisation and the need for the use of health services?

5. Is the intervention cost-effective and might it lead to overall cost-savings?

6. Can a screening questionnaire used in primary care reliably distinguish between low and high risk of falling?

7. Is there any difference in deaths between the two groups?

### Subject definition

The study population will comprise men and women aged 70 and over identified at being at high risk of falling by a postal screening questionnaire, registered with the participating general practices in Nottinghamshire and Derbyshire.

### Exclusion criteria

Patients already attending one of the day hospitals

Patients under follow-up with an existing primary care based falls prevention scheme or day hospital falls service

Residents in nursing or residential homes

Patients with terminal illnesses

Those unwilling or unable to travel to the day hospital (using transport as provided)

## Study design and treatment definition

### Study design

The proposed study is a pragmatic parallel group randomised controlled trial where the participants will be randomised into either the intervention day hospital arm or to a control (current practice) arm. After outcome measurement has taken place those in the control arm will be offered the day hospital intervention.

### Intervention & control groups

The two arms of the study are as follows:

• Intervention arm: screening questionnaire, information leaflet, leaflet on falls prevention and invitation to attend the day hospital for assessment and any subsequent intervention

• Control arm: screening questionnaire, information leaflet, leaflet on falls prevention and usual care from primary care service until outcome data collected, then offer of day hospital intervention.

## Procedures and observations

In most cases, subjects will be contacted by post and telephone at each stage of the study; however, it is likely that some individuals will be unable or unwilling to use these methods in which case they will be offered a home visit.

### Baseline measurements

Participating general practices will be asked to identify all patients aged 70 and over in their practice. Practices will be asked to exclude all those living in a nursing or residential home and those with terminal illness. The remaining subjects will be sent an invitation to participate by their general practice.

The invitation will include the patient information leaflet as well as a screening questionnaire which the subjects will be asked to return to the project officer. This screening questionnaire is based on published guidelines[1] and will be adapted for the local population in a pilot study. Those subjects not participating in the randomised study will be offered the opportunity to complete the monthly diaries only; data from these replies will be used to explore the predictive strengths of the screening questionnaire. The screening questionnaire will enable the identification of subjects deemed to be at high risk of falling and will include questions on previous falls history, mobility, use of walking aids and the number of medications. In addition to returning the questionnaire, subjects will be asked if they would be interested in participating in the study and if so to provide contact details, including phone number. The screening questionnaire will also ask about other exclusion criteria such as attendance at the day hospital. The replies will be analysed by the project officer and suitable participants for the study identified. Potential participants will be asked if they have had contact with either the day hospital or the primary care falls prevention service in the preceding year; in case of any doubt, verbal consent will be obtained to check their possible contact with these services with the day hospital or the primary care team.

A written invitation will be sent offering a home visit from the study nurse where no telephone contact is possible.

Those eligible subjects thought to be at high risk of future falls (approximately 1000) will then be sent a pack containing further information on the study, a falls prevention booklet ('Avoiding slips, trips and broken hips', Department of Health) and a consent pack.

The subjects will then be contacted by phone with the aim of:

• Clarifying any issues about the study

• Confirm responses to the screening questionnaire

• Invitation to take part

• Obtaining verbal consent (based on a standardised schema) and requesting signing and return of consent form in prepaid envelope

On receipt of the signed consent form, the project officer will then contact the randomisation centre. Subjects will be informed of the next steps by phone, with confirmation by post within 48 hours. This second letter will include information on which arm they have been randomised, the diaries for recording falls and if appropriate, an appointment for the day hospital.

For those willing to take part but who do not want to be part of the main RCT, there will be the option of returning a brief falls diary and the end of study questionnaire only.

### Outcome measurements

#### Definition of primary and secondary outcomes

Primary outcome: rate of falling over the 12 month follow-up period.

Falls will be recorded by giving each participant a diary and reply paid envelopes. The definition of a fall given to subjects in this study will be 'inadvertently coming to rest on the ground or other lower level with or without loss of consciousness and other than as a consequence of sudden onset of paralysis, epileptic seizure, excess alcohol intake, or overwhelming external force' (PROFET[11]).

Participants will be asked to record falls in the diary, along with the outcome (saw GP, phoned ambulance, sent to hospital, injuries). The diaries will be mailed back to the research team at the end of every month. Participants will be contacted via telephone by the "blinded" assessor at the end of each month to encourage return of the diary. Falls will be monitored until, withdrawal from study, death or end of 12 month follow up, which ever event occurs first.

Secondary outcomes:

1. Proportion of people with single or recurrent falls (>1)... defined as above

2. Fall-related injuries: fracture, serious sprain requiring immobilisation in plaster, joint dislocations, head injury requiring hospitalisation, and lacerations requiring suturing

3. Disability: Nottingham Extended Activities of Daily Living Scale; Barthel index of daily living; Quality of life: Falls Efficacy Scale and EuroQoL-5

4. Institutionalisation and use of health services: residency and diary information

5. Cost analysis

6. Screening tool... defined by sensitivity/specificity as well as positive and negative predictive values

7. Deaths will be checked against PCT records and measured as proportions

#### Ascertainment of outcomes

The principal method will be self-reporting using the diary. This will contain a section on falls and the outcomes (carried on as usual, called for help, waited for someone to help, called GP, called ambulance, taken to hospital, nature of any injury). Additionally, there will be a section recording health service utilisation, covering primary care contacts and hospital admissions.

The self-reported data will be cross referenced where possible through access to GP records and hospital information systems. For hospital admissions, access to the case notes will be requested and the notes reviewed. This level of information will allow a more accurate ascertainment of events as well as the costs associated. Information on falls-related drug treatment (such as bone protection therapy) will be obtained from the GP records. These data will be collected by the project manager and project officer on standardised forms. The data collection will be subject to internal audit to ensure accurate and consistent data recording and avoid intraobserver and interobserver bias.

Institutionalisation data will be available from practice registers. Those who change practice as a result of changing address will be traced through the primary care trusts.

Disability and quality of life will be self reported by study participants. They will be asked to complete the Nottingham extended activities of daily living scale (NEADL)[24], Barthel index of Daily Living, EuroQol[25] and the falls efficacy scale[26]. These will be posted at the end of one year, along with reply paid envelopes. Non-responders will be sent a written reminder and if necessary a follow-up phone call ('hot pursuit').

EuoQol is included to facilitate cost-effectiveness and cost-utility calculations, but the Falls Efficacy Scale (FES) is a more sensitive measure of quality of life in this population, hence its inclusion[27]. The FES has been validated in the UK as both a face to face and self completed questionnaire[27]. The intraclass correlation coefficient is 0.58, suggesting fair agreement when used as a postal questionnaire. Both the Barthel index and the NEADL are well validated measures of functional ability and can be used as a postal questionnaire[24].

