#### Trial documentation

The documents required to be completed and by whom are highlighted in table 1.

**Table 1 T1:** Trial documentation

**Form title**	**Completed/sent by**
Screening questionnaire	Potential participant
Invitation pack (PIL, falls advice, consent)	Potential participant
No phone letter v1	Project officer
Consent form	Potential participant
Confirmatory letter (randomised group, diary 1, DH appointment)	Project officer
Exclusion letter to pts	Project officer
Diary completion reminder	Project officer
Diary 2–11	Participant
Acute hospital event form/case note abstraction	Project officer
GP event form/case note abstraction	Project officer
Day hospital resource use	Multidisciplinary team
Final outcome pack (FES, NEADL, EuroQoL, diary 12)	Potential participant
Follow-up only falls enquiry	Non-RCT follow up only participant

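### The project officer who obtains and posts each allocation also abstracts GP and hospital events, so the record-based check on injurious falls is at least partly unmasked

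*Protocol article*

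**What the plan says.** **Allocation.** Under Baseline measurements: "On receipt of the signed consent form, the project officer will then contact the randomisation centre". On the confirmation sent afterwards, the same section says: "This second letter will include information on which arm they have been randomised". Table 1 (Trial documentation) lists "Confirmatory letter (randomised group, diary 1, DH appointment" and enters the project officer as the person responsible.

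**Outcome collection.** Ascertainment of outcomes makes the participant diary the principal source. GP records and hospital systems serve as a cross-reference where possible, and case notes are reviewed for admissions. On who does the record work: "These data will be collected by the project manager and project officer on standardised forms". Table 1 gives the project officer "Acute hospital event form/case note abstraction" and the corresponding GP form. The stated safeguards are the standardised forms and an internal audit.

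**Blinding.** Definition of primary and secondary outcomes says that participants are telephoned by a blinded (the article's own inverted commas) "assessor at the end of each month to encourage return of the diary". This is the only use of the word for outcome staff. Table 1 separately lists "Diary completion reminder" against the project officer.

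**The concern.** Participants know their arm, so diary self-report cannot be masked. What can be masked is the staff side: how persistently diaries are chased, how hard records are searched, and how an event found in the notes is classified. If the person doing that work knows the arm, records may be searched or read differently in the two groups without any intent to do so.

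The outcome most exposed is injurious falls, a secondary outcome analysed by logistic regression. Its categories (fracture, sprain immobilised in plaster, dislocation, head injury leading to admission, sutured laceration) are ones for which clinical notes are the natural confirmation. The article itself expects the record review to make event ascertainment more accurate, so it is meant to influence the data. Intervention participants also have a clinical history taken at the day hospital, a record source that control participants will generally lack during follow-up.

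**Working it through.** No arithmetic applies. The check is to set the assigned tasks side by side.

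| Task | Assigned to | Where stated |
|---|---|---|
| Contact with the randomisation centre | Project officer | Baseline measurements |
| Letter naming the arm, with any day-hospital appointment | Project officer | Table 1; content also in Baseline measurements |
| Monthly telephone call about the diary | Blinded assessor, not identified | Definition of primary and secondary outcomes |
| Diary completion reminder | Project officer | Table 1 |
| Hospital event form and case-note abstraction | Project officer | Table 1 |
| GP event form and case-note abstraction | Project officer | Table 1 |
| Collection of record-based data | Project manager and project officer | Ascertainment of outcomes |

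1. *Does the project officer know the arm?* Yes, for every randomised participant. The first two rows cannot be carried out without it.

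2. *Does the same person abstract events?* Yes. The sentence in Ascertainment of outcomes follows directly on one about drug treatment, so its opening words could be read narrowly. Table 1 removes the doubt by giving both event forms to the project officer. The text adds the project manager, whose knowledge of allocation is not stated. Hence at least partly unmasked, and not wholly.

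3. *Do the stated safeguards address this?* No. Standardised forms and audit are aimed at consistency within and between observers. An abstractor can be consistent and still know the arm.

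4. *Who is the blinded assessor?* The role does not appear in Table 1 or under Project management. The only diary reminder in Table 1 belongs to someone who is not blinded. The two passages can be reconciled if the Table 1 item is a posted form and the call is made by another person, but the article does not say so.

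5. *Does this reach the primary outcome?* Only conditionally. Falls are recorded in diaries. The article does not say whether a fall found only in GP or hospital records is added to the count. If it is, arm-aware searching can alter the primary rate. If it is not, that route is closed and only diary chasing remains.

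**The case against.** The strongest reply is that the article never claims blinded outcome assessment. A reader might infer that outcome data are presented as handled by a blinded assessor and that this claim is then broken. The document does not support that: the word covers one telephone call, and the record collectors are named openly with no claim of masking. This part of the reply stands, and the point here is about the assignment of tasks, not a broken promise.

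Three further replies carry weight. First, the diary reminder may be a letter; Table 1 is a list of forms, and for the final questionnaires the article distinguishes a written reminder from a telephone call. The conflict over reminders is therefore probable and not certain. Second, the injury categories are mostly documented diagnoses or procedures, which limits room for judgement, and standardised forms limit it further. That reduces the risk in classification but leaves the question of how thoroughly records are searched in each arm. Third, service use is defined from residency and diary information, so abstraction is a check on it and not its sole source.

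It could also be said that the full protocol may identify the assessor. It may, but the article fixes the project officer's tasks explicitly, and those tasks combine knowledge of the arm with event abstraction whoever makes the calls.

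**Conclusion.** The point holds in a limited form. The person who obtains and sends the allocation is also assigned the abstraction of GP and hospital events, and nothing in the article masks that work. The injury cross-check and classification are open to avoidable arm-aware ascertainment. The blinded assessor needs to be identified and squared with Table 1.

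Two stronger conclusions are tempting and should not be drawn. One is that the primary fall rate is biased: this depends on an unstated rule about falls found only in records, and on unequal diary chasing, of which there is no evidence, since calls are planned for participants without distinction by arm. The other is that all abstracted data are collected by people who know the arm: this is shown for the project officer only.

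The size of the effect cannot be estimated from the document. It gives no information on how many events come from records alone, or on how ascertainment might differ between arms, so any percentage would be an assumption without a source. The conclusion rests on the tasks being carried out as Table 1 and the text assign them. It is worth correcting because the remedy is cheap, not because a large bias has been shown.

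**What to change.** 1. Separate allocation handling from event abstraction among roles the project already has. For example, the study secretary could make the randomisation call and send the allocation letter and appointment. The checks for contamination and concurrent treatment differ by arm, so they should also stay away from whoever abstracts events. Because the project officer also helps prepare day-hospital staff, moving the call alone may not fully mask that person.
2. Alternatively, leave abstraction where it is and have the blinded assessor already planned for the diary calls classify injuries from abstracts with day-hospital references removed.
3. State who the blinded assessor is, and how the monthly call relates to the reminder in Table 1.
4. State that the primary fall count comes from the diaries, with records used to verify injuries and costs, so that falls found only in records cannot enter differently by arm.
5. If masking is not feasible, describe the abstracted outcomes as collected unblinded.

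The cost is a small reallocation of tasks and a few changed lines in Table 1 and the outcome sections. The document does not show whether the secretary has the capacity, so this needs checking. Masking will be imperfect in any case: notes may reveal day-hospital attendance, and participants may disclose their arm on the telephone.

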#### Economic analyses

Cost-effectiveness analysis taking a societal perspective, including NHS, patient and social services support will be carried out using established methods[28]. Incremental cost-effectiveness ratios will be calculated based on the duration of the trial only.

Resource use data will be collected with respect to inpatient and outpatient staff time (Consultants, GP, nurses, physiotherapists, and occupational therapists), Overhead costs, diagnostic tests (radiology and blood services), dressings, medication, transport costs (NHS and private), patient out-of-pocket costs and patient/carer time costs. Resource use data will be collected using a report form abstracting from patient records as well as the patient diaries at monthly intervals throughout the trial for both the intervention and control groups. These data will be cross referenced, where appropriate, with GP records and prescribing systems.

Health and social care resource use data will be valued using published unit cost data[22,23] Social care items will include the number and duration of carer visits per day, and the use of home food delivery services. Time costs will be valued using published wage rates from the new earnings survey and patient out-of-pocket costs will be reported directly by the patient.

The principal outcome measure will be the number of falls prevented to give the incremental cost per fall prevented and Quality Adjusted Life Years as measured on the EuroQol EQ-5D to produce the cost per QALY.

No discounting will be necessary as the trial period is 12 months. One way sensitivity analysis of extremes to test the robustness of the estimated incremental cost-effectiveness ratios will be undertaken.

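### EQ-5D, FES, NEADL and Barthel are read once, at 12 months, so the incremental QALY rests on an unstated baseline and path assumption and these outcomes cannot be baseline-adjusted

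*Protocol article*

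**What the plan says.** Under Ascertainment of outcomes, participants self-report disability and quality of life: "They will be asked to complete the Nottingham extended activities of daily living scale (NEADL)[24], Barthel index of Daily Living, EuroQol[25] and the falls efficacy" scale. The timing follows at once: "These will be posted at the end of one year, along with reply paid envelopes".

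Under Economic analyses, the effect measures are falls prevented and "Quality Adjusted Life Years as measured on the EuroQol EQ-5D to produce the cost per QALY". The horizon is fixed: "Incremental cost-effectiveness ratios will be calculated based on the duration of the trial only".

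Under Univariate and multivariate analyses, disability, quality of life and fear of falling are compared by linear regression, with a concession that some of these comparisons lack power. The same section promises multivariate adjustment if baseline characteristics differ importantly.

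Table 1 (Trial documentation) lists the scales in one form only: "Final outcome pack (FES, NEADL, EuroQoL, diary 12". Barthel is not in that list, although both Outcome measurements and Ascertainment of outcomes name it.

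**The concern.** A QALY over 12 months is utility accumulated across the year. A single reading at the end gives neither the starting level nor the path. The cost-utility analysis, which is part of secondary question 5, therefore depends on something the trial will not observe.

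The same gap touches secondary question 3, on disability and quality of life. The adjustment rule cannot be applied to the starting level of any of the four scales, and the comparisons forgo the covariate most likely to sharpen them. A participant who leaves before the final pack contributes no score on any scale, so a missing-data analysis has no earlier value of the outcome to draw on. A baseline cannot be recovered after randomisation, so no analysis plan can repair this later.

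**Working it through.** The plan gives no figure on this point to reproduce. The check is whether any baseline reading exists, and then what its absence costs.

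**1. Is there a baseline reading anywhere?**

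- Screening questionnaire (Baseline measurements): it "will include questions on previous falls history, mobility, use of walking aids and the number of medications", plus exclusion items. None of the four scales is named.
- Pack sent before consent (same section): study information, a falls booklet and consent papers.
- Letter after randomisation (same section): "This second letter will include information on which arm they have been randomised, the diaries for recording falls and if appropriate", an appointment.
- Monthly diary (Ascertainment of outcomes): falls and their consequences. "Additionally, there will be a section recording health service utilisation, covering primary care contacts and hospital admissions". No utility measure.
- Table 1: FES, NEADL and EuroQoL in the final pack only.

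These descriptions agree: one reading, at 12 months. The participant flow figure is not shown and could not be checked.

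**2. What one reading gives for the QALY**

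Let u0 and u1 be a participant's EQ-5D at baseline and 12 months. On a straight path the individual QALY is (u0 + u1)/2, and u0 is missing.

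Between arms, the QALY difference is (Δ0 + Δ1)/2. Randomisation makes the expected Δ0 zero, so Δ1/2 estimates the difference if the path is straight. With an assumed Δ1 of 0.03:

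- equal start and straight path: 0.03/2 = 0.015 QALY
- full effect present from the first day: 0.030 QALY

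The second figure would halve the cost per QALY relative to the first. The article does not say which path is assumed.

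**3. Chance imbalance in baseline EQ-5D**

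Inputs: 160 per arm (Power and sample size); assumed SD 0.20 to 0.30, equal at both times; assumed correlation ρ of 0.3 to 0.7. The documents give neither SD nor correlation.

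- SE of Δ0 = SD × √(2/160): 0.022 at SD 0.20, 0.028 at 0.25, 0.034 at 0.30.
- 95% range of a chance imbalance = ±1.96 × SE: ±0.044 at SD 0.20 to ±0.066 at SD 0.30.
- A baseline difference carries into Δ1 by the factor ρ, and into Δ1/2 by ρ/2. For a one-SE imbalance at SD 0.25 and ρ = 0.6: 0.028 × 0.6/2 = 0.008 QALY. Across the assumed ranges: 0.022 × 0.3/2 = 0.003 to 0.034 × 0.7/2 = 0.012.
- At SD 0.25, the SE of Δ1/2 is 0.028/2 = 0.014. Adjusting for baseline with ρ = 0.6 gives 0.014 × √(1 − 0.36) = 0.011.

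**4. Precision of the scale comparisons**

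Adjusting for baseline multiplies the variance by 1 − ρ². The detectable difference at 80% power and two-sided 5% is 2.80 × √(2/160) = 0.313 SD without baseline, and 0.313 × √(1 − ρ²) with it.

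| Assumed ρ | Variance factor | Equivalent gain in participants, 1/(1 − ρ²) − 1 | Detectable difference (SD) |
|---|---|---|---|
| 0.3 | 0.91 | 10% | 0.30 |
| 0.5 | 0.75 | 33% | 0.27 |
| 0.6 | 0.64 | 56% | 0.25 |
| 0.7 | 0.51 | 96% | 0.22 |

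**5. Missing data**

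The plan allows 20% attrition: 400 × 0.20 = 80 participants. Any of them lost before the final pack have no score on these scales at any time.

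**The case against.** The best defence is randomisation. It makes baseline utility equal in expectation, so the 12-month comparisons are unbiased apart from missing data, and Δ1/2 is a legitimate estimate of the incremental QALY under a straight path. A two-point area under the curve adjusted for baseline targets the same quantity: its arm coefficient is half the baseline-adjusted coefficient on u1. It also needs the same straight path, which two points cannot test. All this stands. A reader might infer that the cost per QALY cannot be validly computed; the documents do not support that for the difference between arms.

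A reader might also infer that the plan overstates the QALY gain two-fold. That would follow only if the 12-month value were taken as the whole year's QALY and the true divergence were linear. The article never says it will do the former, and an effect that appears early would bring the ratio nearer 1. Deriving the QALY may fairly be left to the analysis plan, which is not shown. That plan can state an assumption, but it cannot supply a reading that was not taken.

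Nor does a chance imbalance pass whole into the result. It carries over in part, and is random error that the confidence interval already covers.

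On precision, the correlation is assumed, and one value need not suit four scales. The intraclass correlation of 0.58 that the article quotes for the FES makes the upper end of the range doubtful for that scale. The screening items could serve as covariates and recover some precision, so the table is the gain over an unadjusted comparison. These points lower the expected benefit but do not remove it.

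Finally, condensing for a journal is not the explanation: the article states when the scales are posted and itemises the forms.

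**Conclusion.** The point holds as a weakness that should be fixed, not one that undermines the trial. The four scales are measured once, individual area-under-the-curve QALYs cannot be formed, and the incremental QALY rests on an equal-baseline, straight-path assumption that the article does not state. For these scales the plan's own rule on adjusting for baseline differences cannot be carried out.

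The size is moderate and depends on assumed inputs. Variance would fall to between 0.91 and 0.51 of the unadjusted value for correlations of 0.3 to 0.7. A one-SE chance imbalance in EQ-5D contributes about 0.008 QALY at SD 0.25 and correlation 0.6 (0.003 to 0.012 over the ranges used). The loss is in precision, adjustment and support for missing-data analysis. The rate of falls, its analysis and the cost per fall prevented are not touched.

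Barthel's absence from Table 1 is a separate and smaller inconsistency. It may be clerical, but if the table were followed literally, a named outcome would not be collected.

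**What to change.** - Add EQ-5D, FES, NEADL and Barthel to the consent pack, to be returned with the signed consent form. Randomisation is triggered by receipt of that form, so the readings would precede allocation.
- Compute each participant's QALY as area under the curve from the two readings, with baseline EQ-5D as a covariate in the arm comparison. State the straight-path assumption, since two readings do not test it.
- Include the baseline score in the linear regressions for FES, NEADL and Barthel.
- Reconcile the final pack in Table 1 with Outcome measurements and Ascertainment of outcomes on Barthel.

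Cost: extra pages in a pack already going to about 1000 people, and data entry for 400. The added burden could slightly lower uptake, and the recruitment plan has no slack: it needs 40% of 1000 to reach 400, so each percentage point lost is 10 participants (1000 × 0.01). The documents give no basis for estimating that effect; the planned Nottingham pilot phase could be used to watch for it.
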